### 4.2.2 Assessments for Treatment and Follow-up Period

#### 4.2.2.1 Visit 1 (Day 0)

Subjects must fast 6 to 10 hours prior to the visit. If the subject fails to fast 6 – 10 hours prior to visit, appointment will be rescheduled to the next possible date. The subjects will be asked to fill in the Activity Induced Fatigue (ACTIF) Scale ACTIF pre. Afterwards the subjects perform the Hand-Grip-Strength-Test, the Symbol Digit Modalities Test (SDMT) and the Beck-Depression-Inventory Fast Screen (BDI-FS). Then the vascular function will be analysed by Vasera and SVA. An intravenous catheter for blood drawings will be placed in the forearm/elbow, 5 minutes prior to first time point for blood drawing. 60 minutes before exercise, the first blood sample will be drawn. Right after the first blood sample has been taken, subjects will receive a single subcutaneous injection of **100mg anakinra or placebo**. Directly after the injection the vascular function will again be analysed by Vasera and SVA. Between blood draws, the IV catheters will be kept patent by a slow infusion of saline. Prior to starting the 1-hour exercise the subject is informed about the procedure. A heart rate monitor is placed around the chest and, at time 0, the subject begins to run, starting with a 5 min warm up period at 2 to 4 km/h under target speed at an incline of 0.5%. After 5 min, and in continuation of warm up, treadmill speed is increased so the subject reaches 75% of VO2max based on heart rate measurements, and this submaximal workload is maintained for the remaining time (approx. 55 min, total running time 60 min).

For blood sampling, we will lower the speed of the treadmill to walking speed in order to be able to draw the blood without any complications. The total exercise time per session will be 60 minutes. After finishing the exercise, the subject will stay on the treadmill for a “cool down” at walking speed for 5 min. For the remaining time, until finishing with the blood drawing, subjects will be seated on a chair. Directly after the exercise and after the last blood drawing (1 hour after finishing exercise) the evaluation of the vascular function by Vasera and SVA will be repeated. After the last time point for blood drawing (60 minutes after exercise) the intravenous catheter will be removed. Since subjects have been fasting prior to the exercise bout, we will provide them with a sandwich and a cold drink after finishing with the last blood drawing. If, 15minutes after the last blood drawing, subjects show no signs of malaise they will be given information concerning their next exercise bout and are free to go. 3-4 hours after finishing exercise subjects will return to the study facility. The subjects will be asked to assess their actual overall, motoric and cognitive condition using the VAS fatigue after exercise visual analogue scale. Afterwards they are asked to fill in the Activity Induced Fatigue (ACTIF) Scale ACTIF post. Then the subjects perform the Hand-Grip-Strength-Test, the Symbol Digit Modalities Test (SDMT) and the Beck-Depression-Inventory Fast Screen (BDI-FS) test. Thereafter the subjects are free to go.

Table 5
Exercise Bout Blood Sample Timepoints and Tasks

| **Timepoints** | **Tasks** |
| --- | --- |
| -65min (before exercise) | Intravenous catheter for blood drawing |
| -60 | Blood Sample Nr. 1, then s.c. study drug injection |
| 0 (start of exercise) | Blood Sample Nr.2 |
| 10 | Blood Sample Nr.3 |
| 20 | Blood Sample Nr.4 |
| 30 | Blood Sample Nr.5 |
| 40 | Blood Sample Nr.6 |
| 50 | Blood Sample Nr.7 |
| 60 | Blood Sample Nr.8 |
| +10 (after exercise) | Blood Sample Nr.9 |
| +20 | Blood Sample Nr.10 |
| +30 | Blood Sample Nr.11 |
| +60 | Blood Sample Nr.12, then removal of i.v. catheter |
| +75 | Subjects are free to go if they show no signs of malaise |

After all procedures for this visit have been completed, subjects should resume medications as previously prescribed.

All exercise will be carried out with a heart rate monitor in order to document and control exercise intensity.

Blood samples will be centrifuged and the plasma stored at -80C prior to being assayed.

The following procedures and assessments will be conducted pre-dose unless otherwise indicated:

- Interim medical history
- Concomitant medications
- Vital signs including pulse, blood pressure (systolic/diastolic), respiratory rate, temperature (oral or tympanic), p02, and body weight. Weight is measured pre-dose to calculate the study drug dose to be administered throughout the study. All vital signs other than weight are recorded within 15 minutes prior to the injection, every 30  10 minutes following the injection until 2 hours after the injection, and immediately prior to the subject’s release. Subjects will not be discharged from the facility on Day 0 until at least 2 hours after the injection and at least 1 hour after vital signs are stable. If a subject experiences an SAE, vital signs may be taken more frequently, per standard institutional practice.
- Activity Induced Fatigue Scale ACTIF pre
- SDMT
- BDI-FS
- Hand-Grip-Strenth-Test
- Retrospective analysis blood sample
- First blood sample
- Study drug administration
- Exercise bout (post-dose)
- AEs (post-dose)

#### 4.2.2.2 Visit 2 [Day 6 ( 3 Days)]

Subjects must fast 6 to 10 hours prior to the visit. If the subject fails to fast 6 – 10 hours prior to visit, appointment will be rescheduled to the next possible date. The subjects will be asked to fill in the Activity Induced Fatigue (ACTIF) Scale ACTIF pre. Afterwards the subjects perform the Hand-Grip-Strength-Test, the Symbol Digit Modalities Test (SDMT) and the Beck-Depression-Inventory Fast Screen (BDI-FS) test. Then the vascular function will be analysed by Vasera and SVA. An intravenous catheter for blood drawings will be placed in the forearm/elbow, 5 minutes prior to first time point for blood drawing. 60 minutes before exercise, the first blood sample will be drawn. Right after the first blood sample has been taken, subjects will receive a single subcutaneous injection of **100mg anakinra or placebo** (crossover from Visit 1). Between blood draws, the IV catheters will be kept patent by a slow infusion of saline. Prior to starting the 1-hour exercise the subject is informed about the procedure. A heart rate monitor is placed around the chest and, at time 0, the subject begins to run starting with a 5 min warm up period at 2 to 4 km/h under target speed at an incline of 0.5%. After 5 min, and in continuation of warm up, treadmill speed is increased so the subject reaches 75% of VO2max based on heart rate measurements, and this submaximal workload is maintained for the remaining time (approx. 55 min, total running time 60 min). For blood sampling, we will lower the speed of the treadmill to walking speed in order to be able to draw the blood without any complications. The total exercise time per session will be 60 minutes. After finishing the exercise, the subject will stay on the treadmill for a “cool down” at walking speed for 5 min. For the remaining time, until finishing with the blood drawing, subjects will be seated on a chair. Directly after the exercise and after the last blood drawing (1 hour after finishing exercise) the evaluation of the vascular function by Vasera and SVA will be repeated.After the last time point for blood drawing (60 minutes after exercise) the intravenous catheter will be removed. Since subjects have been fasting prior to the exercise bout, we will provide them with a sandwich and a cold drink after finishing with the last blood drawing. If, 15minutes after the last blood drawing, subjects show no signs of malaise they will be given information concerning their next exercise bout and are free to go. 3-4 hours after finishing exercise subjects will return to the study facility. The subjects will be asked to assess their actual overall, motoric and cognitive condition using the VAS fatigue after exercise visual analogue scale. Afterwards they are asked to fill in the Activity Induced Fatigue (ACTIF) Scale ACTIF post. Then the subjects perform the Hand-Grip-Strength-Test, the Symbol Digit Modalities Test (SDMT) and the Beck-Depression-Inventory Fast Screen (BDI-FS). Thereafter the subjects are free to go.

After all procedures for this visit have been completed, subjects should resume medications as previously prescribed.

All exercise will be carried out with a heart rate monitor in order to document and control exercise intensity.

Blood samples will be centrifuged and the plasma stored at -80C prior to being assayed.

The following procedures and assessments will be conducted pre-dose, unless otherwise indicated:

- AEs (pre-and post‑dose)
- Concomitant medications
- Muscle soreness
- Vital signs including pulse, blood pressure (systolic/diastolic), respiratory rate, temperature (oral or tympanic), p02, and body weight. Weight is measured pre-dose. All vital signs other than weight are recorded within 15 minutes prior to the injection, every 30  10 minutes following the injection until 1 hour after the injection, and immediately prior to the subject’s release. Subjects will not be discharged from the facility until at least 3 hour after the injection. If a subject experiences an SAE, vital signs may be taken more frequently, per standard institutional practice.
- Activity Induced Fatigue Scale ACTIF pre
- SDMT
- BDI-FS
- Hand-Grip-Strength-Test
- Retrospective analysis blood sample
- First blood sample
- Study drug administration
- Exercise bout (post-dose)
- AEs (post-dose)

#### 4.2.2.3 Visit 3 [Day 12 (9 Days)]

Subjects must fast for 6 to 10 hours prior to the clinic visit. If the subject fails to fast 6 – 10 hours prior to visit, appointment will be rescheduled to the next possible date. After all procedures for this visit have been completed, subjects should resume medications as previously prescribed.

The following procedures and assessments will be conducted:

- AEs
- Concomitant medications
- Muscle soreness
- Vital signs including pulse, blood pressure (systolic/diastolic), p02, respiratory rate, temperature (oral or tympanic), and weight (including calculation of BMI)
- Complete physical exam
- CBC with differential, platelets
- Serum chemistry including sodium, potassium, creatinine, CRP, liver transaminases, fasting plasma glucose, AP, CK
- Retrospective analysis blood sample

#### 4.2.2.4 Early Termination

Subjects who leave the study after receiving any amount of study drug should return to the clinic and complete the evaluations listed below. The reason(s) for a subject’s early termination must be clearly documented in the subject’s medical records and on the appropriate page of the CRF. Subjects must fast for at least 6-10 hours prior to the day of the clinic visit. If the subject fails to fast 6 – 10 hours prior to visit, appointment will be rescheduled to the next possible date. After all procedures for this visit have been completed, subjects should resume medications as previously prescribed.

- AEs
- Concomitant medications
- Vital signs including pulse, blood pressure (systolic/diastolic), respiratory rate, p02, temperature (oral or tympanic), and weight (including calculation of BMI)
- Complete physical exam
- CBC with differential, platelets
- Serum chemistry including sodium, potassium, creatinine, CRP, liver transaminases, fasting plasma glucose, AP, CK
- Retrospective analysis blood sample if subject terminated prior to Day 12

## 4.3 Discontinuation

### 4.3.1 Subject Discontinuation

Subjects may withdraw or be withdrawn from the study at any time.

Subjects who discontinue participation in the study prior to receiving study drug will be replaced. No follow-up or additional procedures will be performed on subjects discontinuing prior to receiving study drug. Subjects who discontinue participation in the study after receiving any amount of study drug will not be replaced. However, when subject non‑compliance could adversely affect the integrity of the analyses, additional subjects may be added to the study.

If a dosed subject discontinues, every effort will be made to complete as many subsequent protocol evaluations as possible. At minimum, a subject will be followed for safety for at least 2 weeks following his final dose of study drug. If a subject discontinues and does not return to the clinic, we will attempt to maintain monthly telephone contact through Day 12. If the subject gives a reason for discontinuation, it will be clearly documented in the subject’s medical records and on the appropriate page of the CRF.

### 4.3.2 Study Discontinuation

This study may be terminated at any time. Reasons for terminating the study may include the following:

The incidence or severity of AEs indicates a potential health hazard to subjects;

Subject enrollment is unsatisfactory

# 5.0 ASSESSMENT OF SAFETY

## 5.1 Safety Plan

Following a comprehensive baseline evaluation, each subject’s safety will be monitored with periodic physical examinations, laboratory tests (hematology, chemistry, urinalysis), and the recording and evaluation of all treatment-emergent AEs.

Once evidence of a clinical and/or laboratory abnormality is noticed, the condition will be treated while trying to determine its cause. The subject will then be followed until the condition resolves or becomes chronic or stable.

Subjects will be instructed about possible acute AEs and allergic reactions, including anaphylaxis, which can occur with exogenously administered foreign antibodies. If such reactions are observed, the subjects should be promptly treated according to standard of care.

## 5.2 Adverse Events

The occurrence of an AE will be determined based on observed or volunteered signs and symptoms, as well as changes in the subject’s physical examination and laboratory results. AEs that occur during the study will be recorded on the appropriate Adverse Event pages of the CRF.

An AE is defined as any untoward medical occurrence (e.g., sign, symptom, disease, syndrome, intercurrent illness, abnormal laboratory finding) that emerges or worsens relative to baseline (Day 0 pre-dose), regardless of the suspected cause. Untoward medical events that occur from the time the subject signs the informed consent form to the time the administration of the drug starts are not considered AEs, and should be recorded under medical history.

All AEs will be evaluated for their seriousness, severity, relationship to study drug, and outcome.

An AE occurring **at any dose** (including overdose) should be classified as **SERIOUS** if:

- It resulted in death (i.e., the AE caused or led to death).
- It was life threatening (i.e., the AE placed the subject at immediate risk of death; an AE should not be classified as life-threatening if it hypothetically might have caused death if it were more severe).
- It required or prolonged inpatient hospitalization (i.e., the AE required at least a 24‑hour inpatient hospitalization or prolonged a hospitalization beyond the expected length of stay; hospitalizations for elective medical/surgical procedures, scheduled treatments, or routine check-ups are not SAEs by this criterion).
- It was disabling (i.e., the AE resulted in a substantial disruption of the subject’s ability to carry out normal life functions).
- It resulted in a congenital anomaly/birth defect (i.e., an adverse outcome in a child or fetus of a subject exposed to the molecule or study drug prior to conception or during pregnancy).
- It does not meet any of the above criteria for a serious AE but may jeopardize the subject or may require medical or surgical intervention to prevent one of the outcomes listed above.

All AEs will be graded for severity according to the National Cancer Institute Common Terminology Criteria for Adverse Events (NCI CTCAE), version 3.0 (available on line at <http://ctep.cancer.gov/reporting/ctc.html>).

The following criteria will be used to assess whether there is a reasonable possibility that the study drug caused or contributed to the AE:

Yes (possibly, probably, or definitely related):

- There is a clinically plausible time sequence between onset of the AE and study drug administration

and/or

- There is a biologically plausible mechanism for study drug causing or contributing to the AE

No (unlikely, unrelated):

- Another cause of the AE is most plausible

and/or

- A clinically plausible temporal sequence is inconsistent with the onset of the AE and study drug administration

and/or

- A causal relationship is considered biologically implausible

## 5.3 Laboratory Tests/Other Evaluations

This study involves various procedures and tests, performed repeatedly throughout the study. If a subject has a clinically significant abnormal laboratory test value that is not an expected result of study drug administration or was not present at baseline (Day 0 pre‑dose), the test will be repeated and the subject will be followed until the test value has returned to the normal range or the investigator has determined that the abnormality is chronic or stable.

All abnormal laboratory results will be evaluated for their clinical relevance. An isolated abnormal laboratory result in the absence of any associated clinical finding may or may not be considered an AE; the evaluation will be based on a consideration of the overall clinical context. An abnormal laboratory result will be considered clinically relevant and recorded as an AE when it is part of a clinical abnormality requiring specific medical intervention or follow-up.

A complete physical examination will be performed at Screening, and on Visit 3. Vital signs will be recorded at specified time points throughout the study (see Appendix 2). Vital sign measurements include pulse, blood pressure (systolic/diastolic), respiratory rate, temperature (oral or tympanic), p02, weight and, at Screening only, height to enable calculation of BMI.

All samples will be stored for at least five years. The subject has the right to eliminate the samples at any time.

## 5.4 Procedures for Eliciting, Recording, and Reporting Adverse Events

AEs will be directly observed or elicited using open-ended or directed questions, and/or volunteered by the subjects.

Muscle soreness and adverse events will be assessed 24, 48 and 72 hours after every exercise bout. There will be no assessment of adverse events (AE) or muscle soreness after screening visit.

**Muscle soreness** will be assessed using a visual analog scale. This scale is standard in rheumatoid arthritis studies with slight adjustments (numbers were added in order to quantify assessment). Participants will be asked to fill out as below:

[figure not shown]

### 5.4.1 Recording Adverse Events

To improve the quality and precision of acquired AE data, the following guidelines will be used:

- Whenever possible, recognized medical terms will be used when recording AEs on the AE pages of the CRF. Colloquialisms and/or abbreviations will not be used.
- If known, the diagnosis (i.e., disease or syndrome) rather than component signs and symptoms will be recorded on AE pages of the CRF. However, signs and symptoms that are considered unrelated to an encountered syndrome or disease will be recorded as individual AEs on the CRF (e.g., if congestive heart failure has not been documented, each symptom in the above example will be recorded as a separate AE).
- AEs occurring secondary to other events (e.g., sequelae) will be identified by the primary cause. A “primary” AE, if clearly identifiable, generally represents the most accurate clinical term to record on AE pages of the CRF. Events occurring secondary to the primary event should be described in the narrative description of the case. For example:

| Orthostatic hypotension |  | Fainting and fall to floor |  | Head trauma |  | Neck pain |
| --- | --- | --- | --- | --- | --- | --- |

The primary AE in this example is orthostatic hypotension.

### 5.4.2 Adverse Events Requiring Expedited Reporting

All SAEs will be carefully monitored throughout the course of the study.

If a fatal and life-threatening SAE is evaluated as a sudden unexpected serious adverse reactions (SUSAR.) Swissmedic and KEK have to be informed without delay and no later than 7 calendar days following awareness that event meets SUSAR criteria. If a non-fatal, non-life-threatening SAE is evaluated as SUSAR then Swissmedic must be informed no later than 15 calendar days following awareness that event meets SUSAR criteria.

For further details see adverse event reporting guidelines in appendix 4.

### 5.4.3 Special Reporting Situations

#### 5.4.3.1 Death

Death is an outcome of an event. The **event** that resulted in the death will be recorded and reported on the AE page of the CRF.

#### 5.4.3.2 Hospitalizations for Surgical or Diagnostic Procedures

The illness leading to the surgical or diagnostic procedure will be recorded as the SAE, not the procedure itself. The procedure will be captured in the case narrative as part of the action taken in response to the illness.

## 5.5 Type and Duration of Follow-up after Adverse Events

### 5.5.1 Post Treatment Follow-up

All subjects receiving any amount of drug will be followed until Day 12. All protocol-defined AEs occurring during the study should be fully evaluated, recorded on the appropriate pages of the CRF, and documented in the subjects’ files.

### 5.5.2 Post Adverse Event Follow-up

All subjects who experience AEs will be followed until the event resolves or until the subject’s participation in the study ends. For those AEs judged to be unrelated to study drug, the outcome at last observation will be recorded on the appropriate pages of the CRF.

Subjects experiencing AEs that were judged to be possibly, probably, or definitely related to study drug will be followed until the events resolve or until the event to be chronic or stable. Resolution of such events will be documented on the appropriate pages of the CRF.

# 6.0 Data Analysis and Statistical Methods

Data will be analyzed for safety and biological endpoints. Safety analyses will include all subjects who received any amount of study drug. Efficacy analyses will include all randomized subjects. Analyses of the population of subjects who completed treatment may also be performed.

Since the sample size is small, only exploratory statistical testing will be performed. Study results will be summarized using primarily descriptive statistics and 95% confidence intervals. Since this is a proof of concept study, evaluating an issue that has never been examined before, it is not possible to perform a power calculation.

## 6.1 Disposition of the Study Subjects and Conduct of the Study

The disposition of subjects will be described with summaries by treatment assignment of the number of subjects enrolled, the number of subjects treated, and the number of subjects for whom study drug was permanently discontinued (including the reasons).

## 6.2 Determination of Sample Size

The sample size (20 subjects receiving treatment) was based on clinical and practical considerations.

## 6.3 Analysis of Treatment Group Comparability

Demographic and baseline characteristics will be summarized by treatment group.

## 6.4 Biological and Clinical Activity Analysis

All randomized subjects will be considered for analysis. Efficacy endpoints will be described using the five-number summary (mean, standard deviation, median, minimum, and maximum) by treatment and study visit. Graphs will also be employed.

The underlying assumptions of the t-test for the treatment group effect will be checked using the residuals from the ANCOVA model. If these assumptions are violated, the Wilcoxon signed ranks test will be used to compare treatment groups.

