# SYNOPSIS

| Protocol Title: | **Role of IL-1** **in the regulation of muscle derived IL-6 during exercise** |
| --- | --- |
| Sponsor/Investigator: | [name], Professor, Division of Endocrinology, Diabetes and Metabolism Department of Internal Medicine  University Hospital Basel, Switzerland |
| Protocol Number: | 10.0 |
| Amendment | 1 |
| Study Phase: | 2 |
| Study Drug: | Anakinra (Kineret) and Placebo |
| Study Population: | Healthy lean males |
| Objective: | Evaluate the regulation of muscle derived IL-6 during exercise and in particular whether it is regulated by the IL-1 system. |
| Program Hypothesis: | Muscle derived IL-6 is regulated by IL-1 vs. independently of the IL-1 system during an acute exercise bout |
| Study Design: | Placebo-controlled, double blind, cross-over, randomized, proof-of-concept |
| Sample Size: | 20 subjects |
| Estimated Start: | July, 2011 |
| Estimated Finish: | December, 2011 |
| No. of Sites: | 1 |
| Mean Study Duration for Subjects: | 36d  (screening visit included) |
| Eligibility Criteria: | Inclusion Criteria  Subjects may be included in the study if they meet all of the following criteria:   - male - non-smoking - apparently healthy - BMI >18 and <26kg/m2 - Age 20-50 years - Regular exercise including a minimum of two runs weekly of a total duration of > 2h - Willingness to use contraceptive measures adequate to prevent the subject’s partner from becoming pregnant during the study. Adequate contraceptive measures include hormonal methods used for two or more cycles prior to screening (e.g., oral contraceptive pills, contraceptive patch, or contraceptive vaginal ring), double barrier methods (e.g., contraceptive sponge, diaphragm used in conjunction with contraceptive foam or jelly, and condom used in conjunction with contraceptive foam or jelly), intrauterine methods (IUD), sterilization (e.g., tubal ligation or a monogamous relationship with a vasectomized partner), and abstinence. |

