# 3.0 Study Design

## 3.1 Description of the Study

This is a randomized placebo-controlled, double blind, cross-over, proof-of-concept study of the effects of IL-1 antagonism on peripheral muscle physiology.

The study will consist of one screening visit followed by 3 study visits. During the first two study visits, the subjects (20 apparently healthy, lean men) will perform a submaximal exercise bout on a treadmill for 60 minutes. In addition, subjects will fill in an Activity Induced Fatigue (ACTIF) Scale before (ACTIF pre) and 3-4 hours after (ACTIF post) exercise. After every ACTIF Scale evaluation the subjects perform a Hand-Grip-Strength-Test, assessing the actual motoric shape. Then the subjects are tested by a neuropsychologist by applying the Symbol Digit Modalities test (SDMT), a cognitive screening-test to assess information processing speed and working memory. To assess depression, subjects will be examed by the Beck-Depression-Inventory Fast Screen (BDI-FS), a short version of the Beck-Depression-Inventory (BDI), depicting different facets of depression. These additional tests are performed to evaluate the impact of fatigue on cognitive, motoric and emotional behavior. Before the Activity Induced Fatigue (ACTIF) Scale after exercise (ACTIF post) is applied, subjects will be asked to evaluate their general, motoric and cognitive condition using the Visual analogue scale (VAS) Fatigue after exercise. Subjects will be randomly assigned into two groups consisting each of 10 subjects receiving study medication in a double-blinded, crossed over manner. Treatment consists of a single subcutaneous injection of 100mg IL-1Ra or placebo at visit 1 and 2.,

[visit 1: IL-1Ra/ placebo; visit 2: placebo/ IL-1Ra (cross-over to day 1);]. See table 1 on page 18.

Additionally the vascular function will be evaluated before the injection of the study medication and 1 hour after the exercise bout. The large arterial stiffness known as cardio ankle vascular index (CAVI) and the pulse wave velocity (PWV) will be measured by an oscillometric sphygmograph (Vasera). Furthermore the small vessels will be examined by taking a picture from the retina to calculate the arteriolar-to-venular-ratio (AVR). To assess overall activity of the participants will be given an activity questionnaire (Aktivitätsfragebogen) at screening (12).

The screening visit and the three study visits will be separated by at least 72 hours and at most 9 days.

.

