### 3.5.2 Treatment Assignment

Subjects who meet the study eligibility requirements and have signed the informed consent will be randomly assigned to receive study medication according to the following chart:

Table 1
Study design

|  | **1** | **2** |
| --- | --- | --- |
| 20 Participants | Group 1: (n=10)  **IL-1Ra** | Group 1: (n=10)  **Placebo** |
| Group 2: (n=10)  **Placebo** | Group 2: (n=10)  **IL-1Ra** |

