## 3.8 Outcome Measures

### 3.8.1 Primary Outcome Measure

The primary endpoint is change in exercise-stimulated IL-6 between group dosed with placebo and anakinra.

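### Section 6.4 does not fit the two-period crossover: it leaves open whether the t-test/ANCOVA is paired, and switches on residuals to a signed-rank test that ignores period

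*Protocol*

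**What the plan says.** The synopsis gives the design as "Placebo-controlled, double blind, cross-over, randomized, proof-of-concept". Section 3.1 adds: "Subjects will be randomly assigned into two groups consisting each of 10 subjects receiving study medication in a double-blinded, crossed over manner". Table 1 in section 3.5.2 shows both groups receiving both treatments, one at each of visits 1 and 2. On size, section 6.2 says: "The sample size (20 subjects receiving treatment) was based on clinical and practical considerations".

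Section 3.8.1 words the primary endpoint as a contrast between groups: "The primary endpoint is change in exercise-stimulated IL-6 between group dosed with placebo and anakinra". The second paragraph of section 6.4 then sets the test: "The underlying assumptions of the t-test for the treatment group effect will be checked using the residuals from the ANCOVA model", followed by "If these assumptions are violated, the Wilcoxon signed ranks test will be used to compare treatment groups". No ANCOVA terms are listed, and study visit is named only for the descriptive summaries. Section 6.3 adds: "Demographic and baseline characteristics will be summarized by treatment group".

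Three other provisions bear on this:
- Section 6.0 puts every randomised subject into the efficacy analyses.
- Section 6.0 also limits testing to exploratory use, promises mainly descriptive results with 95% confidence intervals, and makes no power claim.
- Section 4.3.1 does not replace men who stop after dosing, but allows subjects to be added where non-compliance threatens the analyses.

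**The concern.** In a crossover each man is his own control, and visit 1 and visit 2 may differ for reasons unrelated to treatment. An analysis that fits this design compares treatments within men and allows for period. The rule in 6.4 does not clearly do either.

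- **The branches may not match.** The parametric branch is described in terms of treatment groups, whereas the fallback is a paired test. If the first is unpaired, the two branches use different error terms. If it is paired, the ANCOVA behind it is not defined for this design.
- **The choice is made on the data.** The branch depends on residuals, and no criterion for a violation is given.
- **The fallback ignores period.** This holds on any reading of the paragraph. It also needs both values from each man, which sits badly with including everyone randomised.

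A period effect is not far-fetched. Section 3.1 allows visits 72 hours apart, and section 5.4 follows muscle soreness for 72 hours after each bout. The visit 1 text also lists a vascular measurement straight after the injection that the visit 2 text does not. At stake are the width of the confidence interval for the primary result and, if the sequences end up unequal, its centre.

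**Working it through.** The protocol has no calculation to reproduce. It supplies 20 men, 10 per sequence, and 95% intervals. Everything else is assumed: outcome SD 1 at each visit, within-man correlation ρ, period shift π (visit 2 minus visit 1, in SD units), treatment effect τ, and two-sided 5% tests.

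**1. Cost if the t-test/ANCOVA is unpaired.** 95% CI half-widths:
- unpaired, 20 against 20 values: t(38) × √(2/20) = 2.024 × 0.316 = 0.640
- period-adjusted crossover: t(18) × √(2(1−ρ)/20), with t(18) = 2.101

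| ρ | Unpaired | Period-adjusted | Ratio |
|---|---|---|---|
| 0 | 0.640 | 0.664 | 0.96 |
| 0.3 | 0.640 | 0.556 | 1.15 |
| 0.5 | 0.640 | 0.470 | 1.36 |
| 0.7 | 0.640 | 0.364 | 1.76 |
| 0.8 | 0.640 | 0.297 | 2.15 |

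**2. Cost of a paired analysis without period, at 10/10.** The anakinra-minus-placebo difference has mean τ − π in men given anakinra first and τ + π in the others. Without a period term this spread goes into the error, and the expected variance is 2(1−ρ) + π² × 20/19. At ρ = 0.7 and π = 0.5 that is 0.600 + 0.263 = 0.863. The paired-t interval is then √(0.863/0.600) × t(19)/t(18) = 1.199 × 0.996 = 1.20 times as wide as the adjusted one. At π = 0.25 and π = 1 the ratios are 1.05 and 1.65.

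Simulated power (4000 runs per row, τ = 0.5):

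| ρ | π | Unpaired t | Paired t | Signed-rank | Period-adjusted |
|---|---|---|---|---|---|
| 0.7 | 0 | 0.25 | 0.79 | 0.76 | 0.78 |
| 0.7 | 0.5 | 0.22 | 0.65 | 0.61 | 0.78 |
| 0.5 | 0.5 | 0.27 | 0.48 | 0.44 | 0.56 |

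**3. Bias when the completing sequences are unequal.** With n₁ men completing anakinra first and n₂ completing placebo first, the unadjusted mean difference has expectation

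[n₁(τ − π) + n₂(τ + π)]/(n₁ + n₂) = τ + π(n₂ − n₁)/(n₁ + n₂).

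| Completers | Size of bias ÷ π |
|---|---|
| 10/10 | 0 |
| 10/9 | 1/19 = 0.053 |
| 10/8 | 2/18 = 0.111 |
| 10/7 | 3/17 = 0.176 |
| 10/6 | 4/16 = 0.250 |

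The sign depends on which sequence loses men. As a check at 10/7 with π = 0.5 and τ = 0.50, the formula gives 0.50 − 0.176 × 0.5 = 0.412. The simulation gave 0.414 unadjusted and 0.503 adjusted. An unpaired analysis of all available values would have about half this bias (0.088π at 10/7).

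**4. The switch itself.** Since the protocol gives no criterion, a Shapiro-Wilk test on the within-man differences was used to choose between paired t and signed-rank. With normal data and no treatment effect, at 10/10 and ρ = 0.7, the rejection rate was 0.052 without a period shift and 0.020 with π = 0.5.

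**5. Analysis set.** A signed-rank test uses within-man differences, so a man with one period contributes nothing. Section 6.0 includes him, and section 4.3.1 does not replace him.

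**The case against.** A reader might infer that 6.4 prescribes a parallel-group analysis in which no branch uses period. The document does not support that. It never calls the t-test or ANCOVA unpaired, and the one test it fully identifies is a paired test. The ANCOVA terms could be given in a SAP that is not at hand. The fair statement is that the parametric branch is ambiguous. The loss in step 1 applies only on the unpaired reading, and only if ρ is above zero. Disregard of period is established for the signed-rank branch alone.

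Other strong readings also fail:
- **The estimate is biased as designed.** It is not. At 10/10 the bias is zero, and it needs both a period shift and unequal completion.
- **The signed-rank test is always costly.** Without a period effect it loses almost nothing. The protocol shows no period effect, and both visits share the same fast, timing and heart-rate-set workload.
- **Test-switching inflates false positives.** The simulation did not show this.
- **Testing each of the IL-6 sampling times adds false positives.** The protocol plans no such tests. The choice of IL-6 summary and zero point can properly be left to a SAP.
- **Baseline in 6.3 is compared between the same men.** Sections 3.1 and 3.5.2 use group for the randomised sequences, so 6.3 may already mean by sequence. This is a matter of wording.

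The exploratory status in section 6.0 lowers the stakes of any P value. It does not remove the point, because the promised confidence intervals rest on the same error term.

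**Conclusion.** The point holds at moderate severity. Section 6.4 states a rule that does not fit the design: an undefined t-test/ANCOVA tied, through a data-driven switch without a criterion, to a fallback that ignores period and cannot use men with one period.

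The size depends on which reading and which circumstances apply:
- Precision suffers substantially if the parametric branch is unpaired and values within a man are correlated.
- A paired analysis suffers only if there is a period effect. The loss is then modest for a small shift and material at 0.5 SD.
- Bias is a risk under unequal completion, small at 10/9 and approaching a fifth of the period shift at 10/7.

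All of this rests on assumed correlations, shifts and completion patterns. The protocol supplies none, so the figures are a range of consequences and not a forecast. The reason to act is that a better-fitting rule costs almost nothing.

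**What to change.** Replace the second paragraph of 6.4 with one pre-specified analysis and no test-switching:
- **Outcome:** log of the IL-6 AUC over exercise and recovery. Adjust for baseline by covariate and not by subtraction, because a baseline-subtracted AUC can be zero or negative and then has no logarithm.
- **Model:** fixed treatment, period and sequence, a random man effect, and that period's log pre-dose (−60 min) IL-6 as covariate, using all available periods.
- **Report:** the anakinra/placebo ratio with its 95% CI.
- **Sensitivity analysis only:** a rank-sum test comparing within-man period differences (visit 1 minus visit 2) between the two sequences. The period shift is common to both sequences and cancels. The test cannot be stratified by sequence, since all men in a sequence have the same treatment order. It uses men with both periods only.
- **Section 6.3:** state that baseline characteristics are summarised by sequence.

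The cost is one paragraph of text, about one degree of freedom for period and one for the covariate. The change should be made before unblinding.
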